### Outcomes

3.13

All outcomes will be measured and documented at baseline assessment (Week 1), interim assessment (Week 6), and final assessment (Week 12). The primary outcomes are quality of life, assessed using the Parkinson’s Disease Questionnaire-39 (PDQ-39), the MOS 36-item Short Form Health Survey (SF-36), and the Unified Parkinson’s Disease Rating Scale developed by the Movement Disorder Society Part I (MDS-UPDRS Part I). The second indicator is physical function, which covers Reaction time, Balance, Physical coordination, Flexibility, and Walking capacity.

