#### SF-36

3.14.2

SF-36 (26) is a widely used tool for assessing health status and has been validated across multiple disease populations with strong reliability and validity. It comprises eight dimensions: physical functioning (PF), role physical (RP), bodily pain (BP), general health (GH), vitality (VT), social functioning (SF), role emotional (RE), and mental health (MH).

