### Statistical analysis

3.17

A mixed-effect model will be employed to analyze the experimental data, accounting for individual variability. The model will assess the random effect of participants while adjusting for baseline variables. Baseline characteristics will be compared between groups using appropriate statistical tests (e.g., one-way ANOVA for continuous variables, chi-square test for categorical variables) to ensure group equivalence prior to intervention. If any significant baseline differences are found, they will be adjusted for in the subsequent analyses. To account for differences in exercise intensity and total dose between groups, weekly exercise volume (MET-hours/week) will be calculated and included as a covariate in the mixed-effect model. Intergroup comparisons will be conducted without multiple comparison adjustments. The differences in intervention effects among the three groups will be calculated and expressed as effect sizes with 95% confidence intervals (CIs). For outcome analyses, mixed-effect models will be primarily employed to analyze repeated measures across time points. When analyzing between-group differences at individual time points, one-way ANOVA or Kruskal-Wallis test will be applied, depending on data distribution and normality assumptions. Pairwise post-hoc comparisons will apply Bonferroni correction. All statistical analyses will be conducted using SPSS 26.0 and R 4.0.2, with a significance level of *p* < 0.05.

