### Sample size

3.19

The sample size estimation was based on expected changes in PDQ-39 total score, assuming a minimum clinically significant difference of 5 points between groups. Using a power of 80% (1-*β* = 0.80) and a significance level of 0.05 (two-tailed), the required sample size was calculated using G*Power 3.1. Given an estimated standard deviation (SD) of 10.5 and an effect size of 0.5, the initial calculation suggested 42 participants per group. Considering a potential 15% dropout rate, the final sample size was increased to 50 participants per group, resulting in a total of 150 participants.

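### Two unreconciled multiplicity rules for the pairwise group comparisons, neither of which covers the three unranked primary instruments

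*Protocol article*

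**What the plan says.** All references are to the protocol article.

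- **Statistical analysis (3.17), main model:** "For outcome analyses, mixed-effect models will be primarily employed to analyze repeated measures across time points".
- **Statistical analysis, first rule:** "Intergroup comparisons will be conducted without multiple comparison adjustments". This comes directly after the sentence that adds exercise volume as a model covariate. It carries no limit to a model, visit or outcome.
- **Statistical analysis, second rule:** "When analyzing between-group differences at individual time points, one-way ANOVA or Kruskal-Wallis test will be applied", and the next sentence reads "Pairwise post-hoc comparisons will apply Bonferroni correction". The section closes "with a significance level of *p* < 0.05".
- **Outcomes (3.13):** "The primary outcomes are quality of life", measured with PDQ-39, SF-36 and MDS-UPDRS Part I, without ranking or alpha split. Assessments are at baseline, Week 6 and Week 12.
- **Sample size (3.19):** "The sample size estimation was based on expected changes in PDQ-39 total score", with a 5-point difference, SD 10.5, two-tailed 0.05, 80% power, 42 per group, and 50 per group after allowing for 15% dropout.
- **Subject grouping (3.3):** three arms, 1:1:1: Qigong (QG), conventional exercise (EG) and control (CG).

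**The concern.** In a three-arm trial, the intergroup comparisons include the three pairs QG-CG, EG-CG and QG-EG. One sentence leaves such comparisons uncorrected and another corrects them, and nothing says which applies where. An analysis plan that follows one sentence for a given pair can be read as breaching the other. If this is left open, the threshold for a pairwise claim can be chosen after the p-values are known, and a reader of the results could not tell which threshold had been fixed in advance.

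The second layer is the primary family. Three instruments are primary with equal standing, but only the PDQ-39 total was used for sizing, at an unadjusted 0.05. Both multiplicity sentences concern groups; neither addresses instruments. So even if the conflict were settled in favour of Bonferroni over pairs, the chance of at least one false primary claim would still exceed 5%.

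**Working it through.** **Inputs.** From Sample size: target difference 5, SD 10.5, stated effect size 0.5 (5/10.5 = 0.476), 42 evaluable or 50 randomised per arm. From Subject grouping: 3 arms, hence 3 pairs. From Outcomes: 3 primary instruments. Assumed: correlations between instruments of 0 to 0.7, as the documents give none.

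**The plan's own figure.** The dropout step reproduces: 42/0.85 = 49.4, rounded up to 50. The 42 itself does not: a two-sided two-group t-test at d = 0.5 needs 64 per group. That is a separate matter, and nothing below depends on it; 42 and 50 are used simply as the planned numbers.

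**Step 1: thresholds.** Unadjusted, 0.05 per pair. Bonferroni over three pairs, 0.05/3 = 0.0167.

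**Step 2: smallest significant PDQ-39 difference.** Cut-off = t(1 - alpha/2, 2n - 2) x 10.5 x sqrt(2/n), for a simple two-group t-test.

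| n per arm | SE | Cut-off at 0.05 | Cut-off at 0.0167 | p for an observed 5 points |
|---|---|---|---|---|
| 42 | 2.29 | 1.989 x 2.29 = 4.56 | 2.444 x 2.29 = 5.60 | 0.032 |
| 50 | 2.10 | 1.984 x 2.10 = 4.17 | 2.436 x 2.10 = 5.12 | 0.019 |

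An observed difference equal to the target lies between the two cut-offs at both sample sizes. The cut-offs scale with the SD. At 42 per arm, 5 points falls between them for SDs of about 9.4 to 11.5; at 50 per arm, for about 10.3 to 12.6. Baseline adjustment in the mixed model would change the effective SD and so move the disputed zone, but would not remove it.

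**Step 3: family-wise error.** Simulation under no true difference, 3 pairs x 3 instruments at one visit; ranges run from correlation 0.7 to 0.

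| Rule | One instrument | Three instruments |
|---|---|---|
| All pairs at 0.05 | about 12% | about 25-32% |
| Pairs at 0.05 only after a significant omnibus test | about 5% | about 11-14% |
| Pairs at 0.0167 | about 4% | about 10-13% |

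**Step 4: power.** Two-sided t-test, 42 evaluable per arm:

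- d = 0.5: about 62% at 0.05 and 44% at 0.0167.
- d = 0.476: about 58% and 40%.
- For 80% power at 0.0167 and d = 0.5, about 84-86 per arm are needed before dropout.

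**The case against.** **Sentence order suggests a division of labour.** The unadjusted sentence follows the mixed-model text. The Bonferroni sentence follows the time-point ANOVA/Kruskal-Wallis text, and post-hoc usually means follow-up to such an omnibus test. A reader might infer a flat contradiction; the text does not force one, because this scoped reading is available. It softens the point without removing it: the scope is not stated, and under it the same contrast at the same visit still meets two thresholds, with the main analysis being the uncorrected one.

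**Not every p-value is affected.** A reader might infer that any p-value between 0.0167 and 0.05 is both significant and not. That holds only for pairwise group contrasts. Omnibus, group-by-time and baseline tests are untouched.

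**The highest error rate is not the only one.** The 25-32% assumes pairs are tested without an omnibus gate. The plan neither states nor excludes a gate; with one, the figure is 11-14%.

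**SF-36 need not mean eight tests.** Of the SF-36 the article says "It comprises eight dimensions", and counting each as a primary test would push the error far higher. The documents do not support that count: the sentence describes the instrument's content, PDQ-39 is likewise described by eight domains, and scoring is commonly left to the analysis plan.

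**Some detail may lie elsewhere.** The decisive visit and contrast may be named in a document not shown, so their absence is not held against the plan. What stands is what the article itself states: two unreconciled sentences and three unranked primaries.

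**Conclusion.** The point holds as a failure to reconcile two multiplicity rules, together with a primary family that neither rule covers. It should be settled before unblinding, because it decides the result at the trial's own target: under a two-group t-test with SD 10.5, an observed 5-point difference is significant at 0.05 and not at 0.0167, with 42 or with 50 per arm.

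Across the three primary instruments, family-wise error exceeds 5% under each reading examined, from about 10% to about 32%. Those figures rest on assumed correlations, a single visit and no true difference on any instrument. Which part of the range applies depends on whether pairs are gated or corrected, and the plan does not settle that.

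**What to change.** Before unblinding, replace both sentences with one rule tied to the mixed model. One workable version:

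- Make PDQ-39 total at Week 12, the variable used for sizing, the single primary endpoint.
- Test QG-CG, then QG-EG only if the first succeeds, each at two-sided 0.05. The fixed sequence holds the error for these two claims at 5% without splitting alpha.
- Report EG-CG, Week 6, SF-36 and MDS-UPDRS Part I as secondary, with confidence intervals.
- Limit any Bonferroni correction to post-hoc tests explicitly labelled secondary, so that it does not compete with the fixed sequence.

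If all three instruments or all three pairs are to stay primary, name the whole family and apply Holm or Bonferroni over it. EG-CG may be a reason to do so: EG is also delivered remotely, so that contrast bears on the first objective. If Holm, or Bonferroni over pairs, is kept, restate the power. For Bonferroni over three pairs the starting point is about 44% rather than 62% at 42 evaluable per arm and d = 0.5.

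The cost is more than wording. The primary outcomes are published and the trial is registered, so this means a protocol amendment and a matching registry update. Either two instruments become supportive, or the stated power becomes less favourable.

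### Section 3.17 gives two rules for pairwise comparisons, 3.19 sizes at an unsplit 0.05, and the stated 80% power is reached under neither rule on the printed inputs

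*Protocol article*

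**What the plan says.** Section 3.19 (Sample size) bases the calculation on the PDQ-39 total score, "assuming a minimum clinically significant difference of 5 points between groups", with 80% power and "a significance level of 0.05 (two-tailed"). The remaining inputs are given thus: "Given an estimated standard deviation (SD) of 10.5 and an effect size of 0.5". The result is stated as "the initial calculation suggested 42 participants per group", raised to 50 for 15% dropout. No test is named and alpha is not divided.

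Section 3.17 (Statistical analysis) makes mixed-effect models the main outcome analysis. After describing the model it says that comparisons between groups receive no multiplicity adjustment. For differences at individual time points, "one-way ANOVA or Kruskal-Wallis test will be applied, depending on data distribution and normality assumptions". The next sentence reads: "Pairwise post-hoc comparisons will apply Bonferroni correction". The number of comparisons in the correction is not given. With three groups there are three pairs.

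**The concern.** Alpha per pairwise comparison is 0.05 under one sentence of 3.17 and, if the correction covers the three pairs, 0.0167 under another. Section 3.19 was computed at 0.05. Objectives 2 and 3 rest on the contrasts of the Qigong group (QG) with control (CG) and with conventional exercise (EG), and the text does not settle which threshold applies to them.

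Two things are at stake. If Bonferroni applies, the printed power belongs to a different decision rule. If no adjustment applies, the error rate over the three pairs is well above 5%. Leaving the choice open also allows it to be made after the results are seen.

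**Working it through.** **Inputs.** From 3.19: difference 5, SD 10.5, effect size 0.5, two-sided alpha 0.05, power 80%, 42 per group before dropout, 15% dropout. From 3.3: three groups, 1:1:1. Assumptions made here: two-sample t-test, equal SDs, no gain from baseline or repeated measures, Bonferroni over three pairs only.

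**The plan's own figure.** Dropout reproduces: 42/0.85 = 49.4, so 50. The 42 does not. By the normal approximation, n per group = 2(1.960 + 0.842)²/d².
- d = 0.5: 62.8, so 63 (64 by the t-test).
- d = 5/10.5 = 0.476: 69.2, so 70 (71 by the t-test).

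**Power of one pair.** The noncentrality is d√(n/2), and power comes from the noncentral t-distribution with 2n − 2 degrees of freedom. At n = 42 the noncentrality is 0.5 × √21 = 2.291, or 0.476 × √21 = 2.182. The critical values are 1.989 at 0.05 and 2.444 at 0.05/3 = 0.0167.

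| n per group | d | Power at 0.05 | Power at 0.0167 | Loss (points) |
|---|---|---|---|---|
| 42 | 0.5 | 62.0% | 44.3% | 17.7 |
| 42 | 0.476 | 57.8% | 40.1% | 17.7 |
| 50 | 0.5 | 69.7% | 52.8% | 16.9 |
| 50 | 0.476 | 65.5% | 48.1% | 17.4 |
| 64 | 0.5 | 80.1% | 65.6% | 14.5 |
| 71 | 0.476 | 80.4% | 66.1% | 14.3 |

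The last two rows show that correcting the sample size at 0.05 would still leave about 66% wherever Bonferroni applies. To reach 80% at 0.0167 takes 86 per group (d = 0.5) or 94 (d = 0.476), before dropout.

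**A gated alternative.** Test the three groups together at 0.05 and, only if that is significant, test each pair at 0.05. With exactly three groups this is a closed test: if the groups are not all equal, at most one of the three pairwise nulls can be true, so no further split is needed. Simulation (200,000 trials per setting, normal data, SD 10.5, 42 per group, pooled variance) gives, for a true 5-point QG–CG difference:

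| Rule | EG equal to QG or CG | EG midway | Family-wise error, three pairs, no true differences |
|---|---|---|---|
| Unadjusted pairs at 0.05 | 58% | 58% | 12% |
| Three-group test, then pairs at 0.05 | 50% | 45% | 5.0% |
| Three-group test, then Bonferroni | 40% | 40% | 4.2% |

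The closed test therefore gains about 5 to 10 points over Bonferroni.

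**The case against.** The strongest reply is that Bonferroni was never meant for the comparison that was sized. Mixed models are primary, and the sentence waiving adjustment follows their description. The Bonferroni sentence follows the single-time-point tests and is confined to post-hoc comparisons. On that reading the PDQ-39 contrasts are tested at 0.05, the alpha in 3.19, and a sample size need not power supplementary tests. This is a fair reading, and it rules out a stronger claim that a reader might infer: that the QG–CG and QG–EG contrasts are certain to be judged at 0.0167. The document does not say so. It does not say the opposite either, since both sentences concern comparisons between groups and neither is tied to the primary contrasts.

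Three further points stand.
- That the 80% refers to a pairwise test is an inference. The inputs fit a two-group comparison, but no test is named.
- Most of the shortfall is already there at 0.05 (58% to 62% at 42 per group) and comes from the sample size, not from Bonferroni.
- The planned model adjusts for baseline. If 10.5 is a raw-score SD and the baseline correlation were 0.5, power at 0.0167 with 42 per group would be 53% (d = 0.476) or 58% (d = 0.5). At a correlation of 0.6 it would be 61% or 66%. At 0.05 and a correlation of 0.6 it would be 77% or 81%. So it cannot be said without qualification that a true 5-point effect would more likely than not be missed.

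Bonferroni is also valid and conventional, and it has matching adjusted intervals. Being conservative is not an error.

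**Conclusion.** The point holds as an unresolved choice between two thresholds and a power statement that fits neither on the printed inputs. Wherever Bonferroni over three pairs applies, power is 14 to 18 points below that at 0.05. At 42 completers per group, the unadjusted two-sample power is 58% to 62% at 0.05 and 40% to 44% at 0.0167, against the stated 80%.

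The figures rest on a two-sample comparison with equal SDs and no baseline gain. A correction over more than three comparisons would cost more. A sufficiently strong baseline correlation would raise all of them, but none is stated, and 3.19 does not make clear whether 10.5 is the SD of scores or of changes. The documents do not support reading 0.0167 as the settled threshold for the primary contrasts, nor blaming the whole gap from 80% on Bonferroni.

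**What to change.** 1. In 3.17, replace both the sentence that waives adjustment and the Bonferroni sentence with one rule for the three pairwise contrasts, applying to the mixed model and to single time points. One valid wording: *For each outcome, in the mixed model and at each single time point, the three-group test is done first at two-sided 0.05; only if it is significant are the three pairwise differences tested, each at two-sided 0.05.* Keeping Bonferroni is also acceptable if its scope and divisor are stated. Replacing only one of the two sentences would leave the conflict in place.

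2. In 3.19, name the test and restate the power at 42 completers per group for the rule chosen. For 5 points and SD 10.5 without baseline gain, this is about 58% unadjusted, 45% to 50% for the closed test, or 40% for Bonferroni. If a baseline correlation is relied on, state it and say whether 10.5 is the SD of scores or of changes.

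**Cost.** A few sentences of wording and no added participants, but a less favourable stated power. Under the closed test the 95% confidence intervals stay unadjusted, can disagree with the gated tests, and should be labelled so. That rule covers only the three pairs, not the three primary instruments or the time points, and it does not restore 80% power.

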### Blind method

3.18

Subjects will be randomly assigned to one of three groups (QG, EG, or CG). The details of randomization and allocation concealment are described in Section 3.4.1.

Blinding procedures will be implemented to minimise bias:

Participants will be aware of their assigned intervention, but will not be informed about the details of other group interventions since all remote sessions will be delivered via the remote platform.Outcome assessors will be blinded to group allocation to prevent measurement bias during data collection, and statisticians will be blinded during statistical processing until the final analysis stage.Intervention facilitators will only know their specific group assignment and will not be part of data collection or analysis.

### Sample size

3.19

The sample size estimation was based on expected changes in PDQ-39 total score, assuming a minimum clinically significant difference of 5 points between groups. Using a power of 80% (1-*β* = 0.80) and a significance level of 0.05 (two-tailed), the required sample size was calculated using G*Power 3.1. Given an estimated standard deviation (SD) of 10.5 and an effect size of 0.5, the initial calculation suggested 42 participants per group. Considering a potential 15% dropout rate, the final sample size was increased to 50 participants per group, resulting in a total of 150 participants.

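### The stated inputs do not give 42 per group: a two-sided, 80%-power comparison needs 64 (d = 0.5) or 71 (5 points, SD 10.5)

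*Protocol article*

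**What the plan says.** Section 3.19 gives a complete calculation in G*Power 3.1. It concerns the PDQ-39 total score, described in terms of its anticipated change, "assuming a minimum clinically significant difference of 5 points between groups". Power is 80% and alpha is 0.05, two-sided. The remaining inputs and the result are: "Given an estimated standard deviation (SD) of 10.5 and an effect size of 0.5, the initial calculation suggested 42 participants per group". Then: "Considering a potential 15% dropout rate", "the final sample size was increased to 50 participants per group, resulting in a total of 150 participants".

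The section does not name the test, the pair of groups to be compared or any correlation between repeated measurements. Section 3.17 plans a mixed-effect model adjusted for baseline variables. On multiplicity, it says both that comparisons between groups are unadjusted and that pairwise post-hoc comparisons are Bonferroni-corrected.

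**The concern.** This is not a detail left for an analysis plan. Difference, SD, effect size, power and alpha are all given, so the result can be checked, and it is too small by a wide margin. The effect size also disagrees with the other two inputs: 5/10.5 is 0.476, and 0.5 would correspond to 5.25 points.

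The 80% figure is the trial's main quantitative design claim. The objectives include both an effect of Qigong and its comparison with conventional exercise. A reader who trusts the 80% would give a non-significant result on either contrast more weight against a 5-point benefit than the stated calculation supports.

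**Working it through.** **Inputs (section 3.19).** Difference 5 points; SD 10.5; effect size 0.5; power 80%; alpha 0.05 two-sided; 42 per group; dropout 15%; 50 per group enrolled.

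**Step 1: the dropout step reproduces.** 42/(1 − 0.15) = 49.4, which rounds up to 50 per group and 150 in total. The problem lies only in the 42.

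**Step 2: effect size.** d = 5/10.5 = 0.476.

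**Step 3: required n per group.** The normal approximation is n = 2(z₀.₉₇₅ + z₀.₈₀)²/d² = 2(1.960 + 0.842)²/d² = 15.70/d². The noncentral t gives slightly more.

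| d | Normal approximation | Noncentral t |
|---|---|---|
| 0.5 | 62.8, so 63 | 63.8, so 64 |
| 0.476 | 69.2, so 70 | 70.2, so 71 |

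The shortfall is 64 − 42 = 22 to 71 − 42 = 29 completers per group.

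**Step 4: other simple readings.**
- A one-sided test, contrary to the text, needs 51 (d = 0.5) or 56 (d = 0.476) per group.
- A three-group one-way ANOVA with a 5-point spread and SD 10.5 needs 65 per group for means (5, 5, 0), where f = 0.224. For means (5, 2.5, 0), where f = 0.194, it needs 86 per group.

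None of these gives 42 per group.

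**Step 5: power of an unadjusted two-sided two-sample comparison.** The normal approximation is Φ(d√(n/2) − 1.960). For d = 0.476 and n = 42 it gives Φ(2.182 − 1.960) = 58.8%; the noncentral t gives 57.8%. Noncentral t results:

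| Per arm | d = 0.476 | d = 0.5 |
|---|---|---|
| 42 completers | 57.8% | 62.0% |
| all 50 retained | 65.5% | 69.7% |

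**Step 6: detectable difference.** With 42 per arm, 80% power requires d = 0.619, and 0.619 × 10.5 = 6.5 points.

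**Step 7: what baseline adjustment could add.** Let r be the correlation between baseline and Week 12; the documents give none, so the range is an assumption. If 10.5 is the SD of the score, adjustment multiplies the variance by (1 − r²). If 10.5 is the SD of the change, the score variance is 10.5²/[2(1 − r)]. The adjusted variance is then 10.5²(1 − r²)/[2(1 − r)] = 10.5²(1 + r)/2, a factor of (1 + r)/2. Power for 5 points, 42 per arm, two-sided 0.05:

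| r | 10.5 is score SD | 10.5 is change SD |
|---|---|---|
| 0.2 | 60% | 80% (79.5%) |
| 0.5 | 70% | 70% |
| 0.6 | 77% | 67% |
| 0.7 | 86% | 65% |

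The two columns move in opposite directions as r rises, so the result depends on which SD is meant.

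**The case against.** The strongest reply is that the primary analysis is not an unadjusted t-test. Section 3.17 plans a baseline-adjusted repeated-measures model, and section 3.16 keeps data already collected from participants who withdraw, so fewer than 15% may be lost to the analysis. With a score SD, r = 0.6 and d = 0.5, 42 per arm gives about 81% power. This stands as far as it goes. A reader might infer from the arithmetic that the trial itself has 58% to 62% power. The documents do not support that, because those figures belong to an unadjusted comparison with 42 completers.

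A reader might also infer that only a correlation of about 0.63 or more could justify 42. That holds for 5 points if 10.5 is a score SD, since 42 = 70.2(1 − r²) gives r = 0.63. It fails if 10.5 is a change SD, which the reference to anticipated change makes possible, and it ignores any gain from using Week 6 as well.

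The origin of 42 is open. A three-group ANOVA with f = 0.5 needs 42 in total. A repeated-measures calculation with f = 0.25, three measurements and a correlation of 0.67 to 0.69 can give 42 per group. The text states neither set of inputs, so neither explanation belongs in the correction.

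Bonferroni over three pairs would lower the unadjusted power with 42 per arm to 40% to 44%. Because section 3.17 says two different things about multiplicity, that is conditional and not part of the main claim. Finally, the planned 95% confidence intervals would show whether 5 points is excluded, which limits the harm.

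None of this makes the stated inputs yield 42.

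**Conclusion.** Wrong as written. On the inputs in section 3.19, 42 per group should read 64 (d = 0.5) or 71 (5 points, SD 10.5), and the effect size consistent with the other inputs is 0.476. For an unadjusted two-sided comparison of two groups at 0.05, power is 58% to 62% with 42 completers per arm and 65% to 70% with all 50. This conclusion rests on equal groups, a common SD of 10.5 and no multiplicity adjustment. The power of the planned mixed model is undetermined: it could be below or above 80%, depending on a correlation and a type of SD that the text does not give.

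**What to change.** Keep 150 participants and correct section 3.19. State d as 0.476, name the test and the contrast, give the alpha per comparison (after reconciling the two multiplicity statements in section 3.17), and say whether 10.5 is the SD of the score or of the change. Then do one of the following:

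- **(a)** Replace the 80% claim with the power of an unadjusted two-sided comparison at 0.05: about 58% for 5 points with 42 completers per arm, and 80% for about 6.5 points.
- **(b)** Re-base the calculation on the baseline-adjusted Week 12 PDQ-39 contrast, state the assumed correlation with its justification, and show power over a range of r. Use the factor (1 − r²) for a score SD or (1 + r)/2 for a change SD.

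The cost is protocol wording and no extra participants. The downside is that the stated power may become less favourable.
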